#### Peripheral neuropathy

A modified battery of the pediatric-modified Total Neuropathy Scale (peds-mTNS) will assess lower extremity neurological signs and symptoms, to evaluate their contribution to movement and balance findings. The peds-mTNS comprises three sets of questions on sensory symptoms, pain, motor function and autonomic function, as well as a five-part non-invasive neurological exam, including light touch sensation, vibration sensation, pin sensation, distal muscle strength and deep tendon reflexes [68]. The ped-mTNS demonstrated excellent internal consistency (> 0.9) in school-aged children with chemotherapy-induced peripheral neuropathy [68]. To minimize potential confounding factors of central nervous system signs, plantar (Babinski) and clonus reflexes will also be tested [69, 70].

#### Quality of life (QoL)

The Pediatric Quality of Life Inventory (PedsQL) Generic Core Scales 4.0 comprise 23 items measuring four dimensions of QoL; physical functioning, emotional functioning, social functioning and school functioning [71]. Each item utilizes a 5-point Likert response scale across child self-report and parent proxy-report (0 = never a problem to; 4 = almost always a problem), which will be reversed scored, with higher scores indicating better QoL. The measure consists of three age groups: 5 to 7 years (assessor-administered), eight to 12 years, and 13 to 17 years. The PedsQL will be completed by both parents and participants, with both child- and parent-report total scale scores reporting internal consistency of 0.90 [71]. This measure has demonstrated reliability and validity in samples of healthy children and pediatric patients with acute or chronic health conditions (including cancer) [72–74].

Parents and children will also complete the PedsQL Brain Tumor Module [74]. This disease-specific module includes 24 items encompassing six subscales; cognitive problems, pain and hurt, movement and balance, procedural anxiety, nausea and worry. To ensure all questions are considered age-appropriate, the child-report measure excludes the item “trouble writing school papers and reports”, for ages five to seven. The PedsQL Brain Tumor Module has demonstrated reliability and validity in a sample of children with brain tumors, with internal consistency of 0.78–0.92 for the parent-report score and 0.76–0.87 for child self-report score [73].

#### Fatigue

Pediatric Quality of Life Inventory Multidimensional Fatigue Scale (PedsQL-MFS) will be completed by parents and children, including 18 items encompassing three subscales; general fatigue, sleep/rest fatigue, and cognitive fatigue. The format, instructions and Likert response scale are identical to the PedsQL Generic Core Scales, with higher scores indicating less fatigue. PedsQL-MFS has demonstrated internal consistency, reliability and validity among a diverse sample of pediatric cancer patients (aged 2–18) [74]. Validity has been demonstrated in comparisons with healthy, non-cancer pediatric populations [74].

#### Participation

The Participation and Environment Measure for Children and Youth (PEM-CY) is a 20-item instrument completed by the parent and examines the frequency and level of participation across three settings; home, school and community [75]. For each item, parents will be asked to rate: (1) the frequency of their child’s participation in the stated activity on an 8-point scale (daily to never); (2) how involved their child typically is while participating on a 5-point scale (very involved to minimally involved); and (3) whether the parent would like to see a change in their child’s level of participation (yes/no). If yes, the parent will be asked what kind of change they would like to see on a 5-point scale (more involved to less involved). After each section, parents will be asked to indicate whether certain features of the environment make it easier or harder for their child to participate. This measure has demonstrated reliability and validity in a sample of children and youth with and without disabilities (aged 5–17 years), with acceptable internal consistency [75].

#### Perceived movement competence

The Perceived Movement Skill Competence for Young Children is a pictorial tool that scores a child’s perceived movement competence for fundamental movement skills [76]. It involves the participant looking at picture cards of fundamental movement skills that include six locomotor items (run, gallop, hop, leap, jump, glide) and six object control items (strike a ball, bounce a ball, catch, kick, overarm throw and underarm roll). Each card shows a picture of a ‘poor’ or ‘good’ performance of that skill and the participant will be asked to choose which picture they most identify with. In a sample of 23 children, internal consistency was acceptable (≥0.60) for both locomotor and object control [76]. Test-re-test reliability over a one-week period was excellent (≥0.83) [76].

#### Parameters of body composition

Total body scans using dual-energy X-ray absorptiometry (DXA; Prodigy, GE Medical Systems, LUNAR, Madison, WI, USA) will acquire parameters of bone mineral density (BMD, g/cm^2^) and body composition (total body lean and fat mass, kg) data. Scans of the anterior-posterior spines L1-L4, left and right proximal femur will additionally be acquired. All scans will be performed as per standard protocols in lying supine and analyzed using the manufacturers pediatric software (EnCore version 14.1). Total body lean mass will be calculated as fat-free mass minus bone mineral content. DXA measured parameters of body composition and bone mineral density demonstrate a coefficient of variation of less than 2% [77, 78].

### Sample size and power

To detect the clinically important differences of 5.5 mL/kg/min for Peak *V*O_2_ [79] and 2 points on the COPM [48] with 80% power, a sample of 20 participants per group is required (*n* = 40). This calculation assumes a two-tailed alpha level of 0.05, and standard deviations of 5.5 mL/kg/min and 1.5 points for peak *V*O_2_ [80] and the COPM score [81], respectively. To offset a projected attrition rate of up to 20%, we will recruit and enroll 24 participants per group, providing an overall sample size of 48.

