## Methods

### Study design

This study is a single-center randomized controlled trial. Participants will be randomized into the intervention arm (*n* = 24) or usual care (n = 24). The study will be conducted in accordance with the Standard Protocol Items: Recommendations for Interventional Trials (SPIRIT) guidelines [42]. See SPIRIT Checklist in Additional file 1. Assessments for all participants will be conducted at baseline (T1), immediately post-intervention (12-weeks post baseline) (T2), and at 6-month (T3) and 12-month (T4) follow-up. Each assessment involves: 2 days of testing at a clinic visit, assessor-administered or self-administered (age dependent) child questionnaire, self-administered parent questionnaire, and monitoring of physical activity by accelerometer for 7 days. An overview of the study design, the schedule for enrollment and study assessments is shown in Table 1.

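### The stated 20 per group and the 24 per group enrolled for attrition do not follow from the sample-size section's own inputs; the errors offset, so this is a minor correction and not a power shortfall

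*Protocol article*

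**What the plan says.** All the relevant figures stand in the protocol article under Sample size and power.

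- Differences to detect: "To detect the clinically important differences of 5.5 mL/kg/min" for Peak VO2, and "2 points on the COPM [48] with 80% power".
- Variability: "standard deviations of 5.5 mL/kg/min and 1.5 points", in the same order.
- Error rate: "This calculation assumes a two-tailed alpha level of 0.05".
- Result: "with 80% power, a sample of 20 participants per group is required", that is, 40 in total.
- Attrition: "To offset a projected attrition rate of up to 20%, we will recruit and enroll 24 participants per group", that is, 48 in total.

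The Study design section confirms equal allocation, 24 to each arm. Neither the sample-size section nor the Statistical analysis section mentions a multiplicity adjustment, a correlation or any other factor that would change the required number.

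**The concern.** The paragraph presents a chain: inputs, required number, allowance for loss, number enrolled. Each link can be checked from the page, and two fail. Twenty per group is more than the stated inputs need for 80% power. Twenty-four per group is less than is needed to keep 20 after 20% loss.

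A reader who relies on the paragraph is misinformed in two ways. They would believe that the trial drops below 80% power as soon as fewer than 20 per group remain, and that 24 per group guards against this at 20% loss. Both beliefs are wrong on the section's own numbers. At stake is the accuracy of the stated justification, which will be read again when results are reported and completers are counted against the target of 20.

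**Working it through.** **Inputs** (Sample size and power; allocation from Study design): two-sided alpha 0.05; power 80%; 1:1 allocation; Peak VO2 difference 5.5, SD 5.5, so d = 5.5/5.5 = 1.0; COPM difference 2, SD 1.5, so d = 2/1.5 = 1.33; attrition up to 20%.

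**Step 1: the required number per group.**

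Normal approximation: n = 2(1.960 + 0.842)²/d² = 15.70/d².

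- Peak VO2: 15.70/1.0 = 15.70, rounded up to 16.
- COPM: 15.70/1.778 = 8.83, rounded up to 9.

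Exact two-sample t-test: power is the probability that a noncentral t variable with 2n − 2 degrees of freedom and noncentrality d√(n/2) exceeds the two-sided 5% critical value in absolute size.

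- Peak VO2: the solution is n = 16.71, rounded up to 17. Power is 78.1% at 16 and 80.7% at 17.
- COPM: the solution is n = 9.89, rounded up to 10.

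Peak VO2 governs, so the requirement is 17 per group (34 in total). The stated 20 per group (40 in total) is not reproduced.

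**Step 2: power at the relevant sizes, two-sided alpha 0.05, t-test.**

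| n per group | Peak VO2 | COPM |
|---|---|---|
| 17 | 80.7% | 96.5% |
| 19 | 85.1% | 97.9% |
| 20 | 86.9% | 98.4% |
| 24 | 92.4% | 99.5% |

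**Step 3: other routes to 20 at the stated alpha.**

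- A one-sided test at 0.05 gives 14 for Peak VO2.
- Raising power to 85% gives 18 (normal) or 19 (t). Raising it to 90% gives 22 or 23.
- Requiring 80% power on both outcomes jointly, treating them as independent, does not need 20 either: joint power is 77.9% at 17 per group but already 83.3% at 19.

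**Step 4: the attrition allowance.**

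- The stated figure is reproduced by 20 × (1 + 0.20) = 24.
- The number that leaves 20 after 20% loss is 20/(1 − 0.20) = 25 per group, or 50 in total.
- With 24 enrolled, 24 × 0.80 = 19.2 remain, about 19 per group (48 × 0.80 = 38.4 in total, against 40).

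**Step 5: net effect.**

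- Starting from the true minimum, 17/0.80 = 21.25, so 22 per group (44 in total) would cover 20% loss. The planned 24 exceeds this.
- Put the other way, 24 per group falls to 17 only at a loss of 1 − 17/24 = 29%.
- At 20% loss, the 19 per group remaining give 85.1% and 97.9% power.

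**The case against.** The strongest defence is that nothing is harmed. Under every stated input the trial beats its 80% target even at the full projected loss. The attrition slip amounts to one child per group, and it fails only against a figure of 20 that is itself too high. Planning 20 where 17 is the minimum may simply be rounding or a margin, and if the word required is read as sufficient, the first statement is true. The regression adjusts each outcome for its baseline value, which would add power if the quoted SDs are unadjusted; the article does not say whether they are.

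Most of this stands, and it settles the weight of the point. It does not rescue the wording. The section ties 20 to 80% power without mentioning a margin, and baseline adjustment would lower the required number, not raise it to 20. The 24 does not do what its sentence says, whichever test is used. Condensation into an article explains omissions, but here the figures are printed and disagree.

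A stronger reading is tempting. Two-sided alpha 0.025, half of 0.05 for each of the two primary outcomes, gives 19.01 by the normal approximation, which rounds up to 20. A reader might infer an unreported split of alpha, in which case Peak VO2 power would be 79.3% at 20 per group and 76.8% at 19, before any gain from baseline adjustment. The document does not support this. It states 0.05 and mentions no split, the exact t-test at 0.025 gives 21 and not 20, and a numerical near-match is not evidence of the method used.

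**Conclusion.** The point holds as a minor correction of stated figures. At the stated alpha and 80% power, the minimum is 17 per group for Peak VO2 and 10 for the COPM. Twenty per group is therefore 3 more than required and gives about 87% and 98% power. Twenty-four per group is one fewer than the 25 needed to retain 20 after 20% loss, and leaves about 19.

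It would be wrong to conclude that the trial is underpowered: on its own inputs it has about 85% (Peak VO2) and 98% (COPM) power at full projected attrition. This rests on the printed differences and SDs, two-sided alpha 0.05 for each outcome, equal loss in the two arms and an unadjusted two-sample t-test. No baseline correlation is given, so no gain from covariate adjustment is counted.

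**What to change.** Keep 48 participants and reword the paragraph along these lines:

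*At two-sided alpha 0.05, 17 per group (Peak VO2) and 10 per group (COPM) give 80% power. Enrolling 24 per group with up to 20% attrition leaves about 19 per group, giving about 85% power for Peak VO2 and 98% for the COPM.*

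If 20 per group was derived from a different alpha or another design factor, state that basis instead, with the power it gives at 20 and at 19 per group. Leave the attrition projection at 20%: it is a planning assumption and should not be lowered to make 24 fit.

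The cost is a few sentences, with no extra participants and no change to the design or analysis.

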### Statistical analysis

Analysis will follow standard principles for randomized controlled trials using two-group comparisons including all participants on an intention-to-treat basis. Between-group differences on the primary and secondary outcomes will be tested immediately post-intervention and at 6- and 12-month follow-up assessments using linear regression, with treatment group (exercise vs. usual care control) as the main effect and baseline measures of the respective outcome, along with other potential confounders (e.g., age, sex), as covariates.

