### Randomization, allocation, and blinding

The treatment allocation schedule will be generated and supervised by an independent statistician and concealed in Research Electronic Data Capture (REDCap). Using the randomization module in REDCap, participants will be randomized into the intervention or usual care group, stratified by treatment type (surgery only; surgery and radiation therapy; surgery, radiation therapy and chemotherapy). Within an exercise intervention, it is not possible to blind either therapist or participant; however, therapists will not take part in post-intervention outcome assessments. Trained assessors blinded to group allocation will collect outcome data.

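### The regression model does not name treatment type, the factor that stratifies randomization; leaving it out would make the test mildly conservative, and naming it costs almost nothing

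*Protocol article*

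**What the plan says.** In the protocol article, the section on randomization, allocation and blinding says that allocation is "stratified by treatment type (surgery only; surgery and radiation therapy; surgery, radiation therapy and chemotherapy", which gives three strata. It gives no reason for choosing this factor, no expected stratum sizes and no block scheme.

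The Statistical analysis section tests group differences at each of the three post-baseline visits "using linear regression, with treatment group (exercise vs. usual care control) as the main effect", adjusting for "baseline measures of the respective outcome, along with other potential confounders (e.g., age, sex), as covariates". Age and sex are the only covariates named besides the baseline value. Treatment type appears in the randomization section but not in the analysis section.

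The Sample size and power section plans for "clinically important differences of 5.5 mL/kg/min for Peak *V*O_2_ [79] and 2 points on the COPM [48] with 80% power", with "standard deviations of 5.5 mL/kg/min and 1.5 points for peak *V*O_2_ [80] and the COPM score [81], respectively", and concludes that "a sample of 20 participants per group is required", that is, 40 analysed.

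**The concern.** Balancing the arms within treatment type removes the variation between treatment types from the true sampling error of the group difference. A model without treatment type does not know this. It leaves that variation in its residual, so the reported standard error exceeds the true one, confidence intervals are too wide and p-values too large. Adding the stratum terms restores agreement between the two. This is the usual reason for analysing a trial by the factors used to randomize it.

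What is at stake is precision. In a trial of about 40 evaluable children there is no reason to give any away when the variable is known for every child at randomization. The question is how much would be given away under the model the article describes, which already adjusts for the baseline value.

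**Working it through.** **1. The plan's own figure.** Per-group n = 2(1.960 + 0.842)²/d². For Peak VO2, d = 5.5/5.5 = 1.0, so n = 15.7, or 16 (17 with the t distribution). For the COPM, d = 2/1.5 = 1.33, so n = 8.8, or 9. The stated 20 per group is more than these inputs require; it gives 87% power (t) for Peak VO2 and 98% for the COPM. That difference does not bear on this point. What carries forward is N = 40 and a planned effect of 1 SD.

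**2. Inputs the documents do not give.** These are assumed: the share of outcome variance due to treatment type (10–30%), the baseline to follow-up correlation ρ (0.5–0.8), strata of roughly equal size, and close balance within strata.

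**3. Case A: treatment type explains a share r² of the variance left after baseline adjustment.** The ratio of model SE to true SE is 1/√(1 − r²). The true type I error is 2[1 − Φ(1.96/√(1 − r²))].

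| r² | SE too large by | Type I error, formula | Type I error, simulated at N = 40 |
|---|---|---|---|
| 0 | 0% | 5.0% | 4.7% |
| 0.10 | 5.4% | 3.9% | 4.0% |
| 0.20 | 11.8% | 2.8% | 3.0% |
| 0.30 | 19.5% | 1.9% | 2.2% |

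With the stratum terms in the model, simulated type I error is 4.8–5.1% throughout. At r² = 0.20 the model SE is 0.320 SD against a true 0.290 without the stratum, and 0.286 against 0.287 with it.

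**4. Case B: treatment type shifts baseline and follow-up equally, with share R of the variance of each.** Baseline adjustment then already removes most of the stratum effect. On a unit-variance scale the model's residual variance is 1 − ρ². The part of it lying between strata is R(1 − ρ)². So

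model SE / true SE = √[(1 − ρ²) / (1 − ρ² − R(1 − ρ)²)].

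- Largest effect in the range (ρ = 0.5, R = 0.30): √(0.75/0.675) = 1.054, so the SE is 5.4% too large and type I error is 3.9%.
- Middle (ρ = 0.7, R = 0.20): √(0.51/0.492) = 1.018, type I error 4.6%.
- Smallest (ρ = 0.8, R = 0.10): √(0.36/0.356) = 1.006, type I error 4.9%.

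Compared with the SE from the model that includes the stratum, rather than with its own true SE, the gap is 0.6–8.0%, because adding the stratum also sharpens the baseline slope. One baseline-adjusted simulation at N = 40 gave type I error of about 3.6–4.6%. Two others gave 3.8–5.1% and 4.1–5.0%. Monte Carlo error is about 0.2–0.35 points per cell, since √(0.05 × 0.95/12,000) = 0.002 and √(0.05 × 0.95/4,000) = 0.0034.

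**5. Power at 1 SD, N = 40, without and with the stratum (simulated).**

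| Setting | 10% share | 20% share | 30% share |
|---|---|---|---|
| Case B, ρ = 0.5 | 94.0 → 94.3% | 94.2 → 95.1% | 95.2 → 96.8% |
| Case B, ρ = 0.7 | 98.8 → 98.9% | 98.8 → 99.0% | 99.1 → 99.2% |
| Case A, ρ = 0.5 | 94.7 → 95.4% | 95.4 → 97.4% | 96.2 → 98.6% |
| Case A, baseline explains nothing | 87.0 → 89.4% | 88.1 → 92.0% | 89.2 → 95.0% |

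The last row is an outer bound. It applies only if baseline does not predict follow-up, or if the stated SD of 5.5 is already the SD after baseline adjustment. Otherwise the gain is about 0–2 points. If treatment type explains nothing, adding it costs nothing visible: 85.7% against 85.5%.

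**The case against.** The strongest reply is that the covariate list is open. Age and sex are examples, so treatment type may well be among the other covariates, and an analysis plan that is not shown may say so. This stands in part: the article does not name the stratification factor, and it cannot be said to exclude it. Since the article writes the model out and gives examples, it is still fair to ask that the factor used at randomization be named.

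A second reply is that baseline adjustment takes up most of what the stratum would explain, and that leaving it out errs on the safe side. This also stands, and it is why the figures above are small.

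A reader might infer more than the documents support:

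- **That the standard errors will be too large.** This requires both that the stratum is left out and that it predicts outcome beyond baseline. The documents establish neither.
- **That the trial loses substantial power.** Unadjusted power for Peak VO2 at 20 per group is already 87% against a target of 80%, and the stated model adjusts for baseline.
- **That the open list means covariates will be chosen after seeing the data, favouring the intervention.** The article does not say this. Picking the smallest p-value from eight models (age, sex and treatment type each in or out) would raise type I error to 6.7–10.9% in simulation. That is a worst case for a practice that nothing in the text describes, and fixing the final list is ordinary content for an analysis plan.
- **That treatment type was chosen because it is prognostic.** The article gives no reason for the stratification.

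**Conclusion.** The point holds as a modest one. The randomization section stratifies by treatment type and the written-out model does not name it. If it is left out, the consequence is a conservative test: no bias in the treatment estimate and no excess of false positives. Under the stated baseline-adjusted model with 40 analysed and assumed shares of 10–30%, type I error is about 3.6–4.9% when treatment type acts equally on baseline and follow-up, and about 2–4% when the share is of variance beyond baseline. Power gained by adding it at the 1 SD effect is about 0–2 points for a baseline correlation of 0.5 or more. It reaches 2–6 points only if baseline adjustment has not reduced the assumed SD. For the COPM, planned at 1.33 SD, there is next to nothing left to gain.

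These sizes rest on assumed prognostic strength, correlation and stratum sizes. The direction does not. The open covariate list is not a separate fault on this evidence.

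**What to change.** State the primary model as: outcome ~ group + baseline value of the outcome + treatment-type stratum (three levels, as recorded at randomization) + age + sex. Use the same model for both primary outcomes. Put any further covariates in a sensitivity analysis labelled as such. If a separate analysis plan already says this, bring the two texts into line.

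The cost is one sentence and two degrees of freedom. With 40 analysed, the model with intercept, group, baseline, age and sex leaves 40 − 5 = 35 residual degrees of freedom, and adding two stratum terms leaves 33. The stratum is known for every child at randomization, so no new data are needed.
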